### Outcome measurement

Baseline questionnaires are sent after inclusion, which is as soon as possible after patients have consulted their GP. Outcome of intervention will be assessed at 4 and 9 weeks after randomisation; however, if the treatment is not finished at 9 weeks, the patients will receive an additional questionnaire (Ts) after finishing the treatment. Follow-up assessments are planned at 26 and 52 weeks after randomisation.

All outcome measures are reported by means of mailed questionnaires. Table 2 presents the outcome variables, the instruments used and the moments at which they are measured.

Primary treatment outcome of this study is the global perceived effect, which is used to assess recovery from the complaint [31]. In addition, the global perceived effect in daily functioning was explored in order to also establish impact of treatment on daily activity. Both treatment outcomes (recovery of complaint and functioning in daily activity), are assessed on a 7-point Likert-scale, ranging from completely recovered (1) to worse than ever (7).

Costs are measured using a combination of questionnaires to collect data on direct medical costs (e.g. the amount of received treatment and additional therapy received), and indirect costs due to sick leave and disability.

Secondary outcome measures include main complaints, pain intensity, medical consumption, coping, functional status, quality of life, and psychological variables. Prognostic factors are measured including demographic variables, the baseline variables and the psychological variables (table 2).

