### Analyses

Descriptive statistics will be used to examine comparability of baseline data between PT and GAP, and to check if randomisation was successful. Before this analysis, decisions about differences considered to be clinically relevant are made and, if necessary, adjustment will be made for these differences in multivariate analysis. Further, all outcome data will be screened for normality and, if necessary, logarithmic transformations or non-parametric methods of analysis will be applied.

The first aim is to evaluate the clinical and cost effectiveness of GAP compared to PT. Clinical effectiveness will be examined with a Student's t-test (continuous), a Chi-square test (dichotomised) or a Wilcoxon test (not normally distributed) according to the intention-to-treat principle. This means that patients will be analysed in the treatment group to which they are randomly allocated. For missing data, imputation techniques will be used. When the dropout rate is 10% or more, or loss to follow-up is 20% or more, per-protocol analysis will be performed. The results on primary outcome will be dichotomised into improved versus not improved. Improved implies completely recovered and much improved, whereas not recovered implies slightly improved, not changed, slightly worsened, much worsened, and worse than ever [31].

Cost effectiveness will be calculated from a societal perspective. Costs (direct as well as indirect) will be related to the treatment effects, based on the primary outcome measure, by calculating cost-effectiveness ratios.

The second aim is to identify subgroups of patients that benefit most from one of the two treatments. The following subgroups will be investigated: duration and severity of the complaint, depression, and fear of movement.

The third aim is to identify important variables for recovery. For this purpose multivariate analysis will be performed to investigate the influence of prognostic variables and patient characteristics on the outcome. Separate analyses will be conducted to investigate prognostic factors for short-term (3 months) and long-term (12 months) recovery.

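### The between-arm tests are valid but inefficient: neither the baseline score nor the stratification factors are pre-specified, and adjustment and choice of test depend on the data

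*Protocol article*

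**What the plan says.** All references are to the protocol article.

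- **Test.** Analyses: "Clinical effectiveness will be examined with a Student's t-test (continuous), a Chi-square test (dichotomised) or a Wilcoxon test (not normally distributed", under intention to treat, so "patients will be analysed in the treatment group to which they are randomly allocated".
- **Adjustment.** Baseline data are compared between the arms. What counts as a clinically relevant difference is settled before that comparison, and then "if necessary, adjustment will be made for these differences in multivariate analysis".
- **Scale.** All outcome data are screened for normality and, "if necessary, logarithmic transformations or non-parametric methods of analysis will be applied".
- **Missing data.** "For missing data, imputation techniques will be used". The same section adds: "When the dropout rate is 10% or more, or loss to follow-up is 20% or more, per-protocol analysis will be performed".
- **Visits.** Outcome measurement: there is a baseline questionnaire, then "Outcome of intervention will be assessed at 4 and 9 weeks after randomisation", with an extra questionnaire if treatment runs past 9 weeks. "Follow-up assessments are planned at 26 and 52 weeks after randomisation".
- **Stratification.** Randomisation: allocation is in blocks of six within strata of gender, age and severity of the complaint, which the section describes as important prognostic factors.
- **Primary outcome.** GPE is a 7-point rating of recovery, dichotomised into improved or not. The Sample size section plans 80 per arm for a 20% difference in GPE at 9 weeks.

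**The concern.** The plan collects a baseline questionnaire and stratifies on three factors it regards as prognostic, but commits to none of this information in the comparison of the arms. Whether a covariate is used depends on the imbalance that happens to appear. A strongly prognostic baseline score that is well balanced would therefore never enter, although it would sharpen the estimate just as much.

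The normality screen adds a second data-dependent choice. One instrument could be reported as a mean difference, a ratio after log transformation, or a rank comparison, depending on how the data look. This sits awkwardly with the aim, in the section on why a design article is published, of limiting data-driven analysis.

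At stake is the precision of the secondary outcomes, and a primary test that does not take credit for the stratification.

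**Working it through.** **1. The plan's own figure.** The stated size is 160 (80 per arm) for a 20-point difference with 80% power. Alpha, sidedness and the two group rates are not given, so the figure cannot be uniquely reproduced. Assume two-sided 0.05, no continuity correction, and

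n per arm = [1.96·√(2p̄(1−p̄)) + 0.842·√(p₁(1−p₁)+p₂(1−p₂))]² / (p₂−p₁)²

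- 20% v 40%: (1.270 + 0.532)² / 0.04 = 81.2, so 82 per arm, 164 in total. By symmetry 60% v 80% is the same.
- 30% v 50%: 93 per arm, 186 in total.
- 40% v 60%: 97 per arm, 194 in total.

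The stated 160 is close to the first case. What matters here is that the plan sizes the trial on a difference between two proportions.

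**2. Continuous outcomes with a baseline score.** With correlation r between baseline and follow-up, adjusting for baseline multiplies the variance of the treatment difference by (1−r²). The interval width is multiplied by √(1−r²), and 160·(1−r²) adjusted patients match 160 unadjusted. The article gives no r, so a range is assumed.

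For power, take the standardised difference that an unadjusted comparison of 80 per arm detects with 80% power: (1.960 + 0.842)·√(2/80) = 0.443. Adjusted power is Φ(2.802/√(1−r²) − 1.960).

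| Assumed r | √(1−r²) | Interval narrower by | Equivalent N for 160 | Power at 0.443 SD |
|---|---|---|---|---|
| 0 (unadjusted) | 1 | 0% | 160 | 80.0% |
| 0.3 | 0.954 | 4.6% | 146 | 83.6% |
| 0.5 | 0.866 | 13.4% | 120 | 89.9% |
| 0.7 | 0.714 | 28.6% | 82 | 97.5% |

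If 20% were lost (64 per arm), power for the same 0.443 SD would be 70.7% unadjusted and 82.5% adjusted at r = 0.5.

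**3. GPE.** It rates perceived change, so there is no pre-treatment value and step 2 does not apply. Blocking within strata balances gender, age and severity by design. The ordinary chi-square test still counts the variation they explain as noise, so its standard error tends to be too large. The size of this depends on how strongly the strata predict GPE, which the article does not say.

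**4. Attrition.** A simulation (4,000 runs, 80 per arm, true difference 0.40 SD, assumed correlations of 0.5 with baseline and 0.7 between follow-up visits, about 17% lost depending on the earlier visit) compared a two-sample analysis of observed cases with a model using baseline and the earlier visit.

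| Loss | Observed cases: mean (SE) | Model: mean (SE) |
|---|---|---|
| Same direction in both arms | 0.38 (0.172) | 0.40 (0.148) |
| Opposite directions by arm | 0.58 (0.173) | 0.40 (0.148) |

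The observed-case standard error is about 16% larger (0.172/0.148 = 1.16). Its bias is small in the first row and large only in the second. Neither row represents the plan, because the plan imputes.

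**The case against.** The case for leaving the plan as it is has several sound parts.

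- **Baseline is not ignored.** A reader might infer that from the list of tests, but conditional adjustment is planned, with relevance decided beforehand. This stands. The criticism is narrower: adjustment triggered by imbalance is weaker than a pre-specified covariate.
- **Bias at 26 and 52 weeks is not shown.** A reader might infer that simple tests make the long-term results biased by drop-out. Imputation is planned and could use baseline and earlier visits. Neither an observed-case analysis nor carrying the last value forward is named. The large bias in step 4 also needs loss in opposite directions by arm, for which the article gives no support.
- **The 20% is not a forecast.** Loss of that size is only a trigger for a per-protocol analysis.
- **The gains in SD units do not reach the primary outcome.** This stands: GPE has no baseline score.
- **Some of the reading is inference.** Separate tests at each visit, and a test that changes between visits, are likely but not stated. The table setting out which outcome is measured when is not in the text at hand.
- **A condensed article may leave models to a fuller plan.** This is true of covariate lists and imputation detail. Here, however, the article does name its tests and its rule for adjustment, and those can be improved as stated.

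**Conclusion.** The point holds as one of efficiency and pre-specification, not validity. Unadjusted tests after stratified randomisation remain valid.

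For continuous secondary outcomes with a baseline score, the plan gives up about 5% to 29% of interval width at assumed correlations of 0.3 to 0.7; at the low end this is minor. For GPE, the unstratified test tends to be conservative by an amount that cannot be calculated from the article. Attrition bias is a possibility that turns on the unnamed imputation method. The two data-dependent choices (adjust or not, which test or scale) add avoidable flexibility. The change is worth making because it uses data already collected.

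**What to change.** **Continuous outcomes with a baseline score.** Pre-specify as the main analysis a linear mixed model over the visits scheduled for that outcome (a plain linear model if there is only one), with treatment, visit, treatment-by-visit, baseline score, gender, age and severity. Use it whatever the imbalance check or normality screen shows, with a bootstrap interval if residuals are skewed. Report the treatment difference at each visit.

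**Dichotomised GPE.** Use an analysis adjusted for the stratification factors that reports a risk difference at each visit, for example Mantel-Haenszel or standardised logistic regression. This matches the 20% difference in the Sample size section. A logistic mixed model is less suitable because its subject-specific odds ratio leaves that scale. If each factor has two levels (an assumption), there are 2×2×2 = 8 strata averaging 160/8 = 20 patients, which is workable.

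**Simple tests.** Keep the t, chi-square and Wilcoxon tests as a check.

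**Cost.** Revised wording, slightly more programming and a less simple results table. No new data are needed.

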### Sample size

The sample size for this study is calculated according to the global perceived effect (GPE). Based on previous studies, a 20% difference in GPE is expected after completion of either treatment (9 weeks) and is considered to be clinically relevant; 160 patients are needed to detect this difference. In this calculation a power (1 - β) of 80% is taken into account. Thus, the inclusion of 80 patients per treatment group is planned.

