### Randomisation

An independent examiner using a computer-generated randomisation schema performs randomisation. To prevent unequal distribution, patients are pre-stratified based on three important prognostic factors: gender, age and the severity of the complaint, which are recorded at baseline [27]. Further, unequal group sizes are prevented by using a 6-block randomisation that equalizes allocation to the two treatment groups per stratum after every sixth patient [28]. After randomisation, patients choose a physiotherapist within the allocated treatment group. Then, to ensure that the treatment starts as soon as possible, the research assistant makes the first appointment for treatment.

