### Physiotherapists and Interventions

After receiving written information, 34 physiotherapists in region West Brabant will participate in either the physiotherapy treatment (PT) or the graded activity programme (GAP). To optimise the contrast between the two treatments, both groups are strictly separated throughout the study. The PT group consists of 16 physiotherapists and the GAP group of 18 physiotherapists. The PT physiotherapists participate in a meeting to standardize the physiotherapy treatment. The GAP physiotherapists are instructed on the behavioural graded activity approach during a two-day theoretical and practical training course.

Both interventions are performed in an outpatient setting. A maximum of 18 treatments per patient is set and each treatment takes about 30 minutes, which is in accordance with medical insurance policy in the Netherlands. Before treatment starts, physiotherapists receive a completed questionnaire about the patient's main complaints [29]; this questionnaire reveals the three daily activities which are considered the most important complaints to the patient. Physiotherapists can use these three activities in the process of formulating the patient's primary therapy aim. In both treatments, the physiotherapist starts with a physical examination of the patient and an anamnesis. Then an individually tailored program will be applied and the process recorded after each treatment session using a specially designed form.

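### Therapists are nested within arm, but effectiveness is tested as if patients were independent, which understates the standard error for any positive therapist ICC

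*Protocol article*

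**What the plan says.** Protocol article, Physiotherapists and Interventions: "The PT group consists of 16 physiotherapists and the GAP group of 18 physiotherapists". The two groups are kept apart throughout, so no therapist treats patients of both arms. Therapists tailor the programme to the individual patient.

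Protocol article, Randomisation: "After randomisation, patients choose a physiotherapist within the allocated treatment group". Nothing there balances caseloads.

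Protocol article, Sample size: "the inclusion of 80 patients per treatment group is planned", based on a 20% difference in global perceived effect (GPE) and 80% power. No allowance for clustering is mentioned.

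Protocol article, Analyses: clinical effectiveness is examined with a Student's t-test, "a Chi-square test (dichotomised) or a Wilcoxon test (not normally distributed) according to the intention-to-treat principle". The primary outcome is dichotomised, so the chi-square test applies to it. The only adjustment foreseen for the treatment comparison is for relevant baseline differences. Therapist, clustering and ICC appear nowhere in the article.

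**The concern.** Because no therapist crosses arms, differences between therapists do not cancel out of the comparison; they become part of it. A few unusually good or poor therapists in one arm shift that arm's result, and a test that counts 160 independent patients does not allow for this. The trial wants to draw a conclusion about two approaches, not about the particular 34 people who deliver them.

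A therapist effect is plausible here. Tailoring, the choice of techniques in PT, and joint quota setting and reinforcement in GAP all leave room for it, and the Discussion counts the therapist's approach to the patient as part of the contrast. P-values that are too small and intervals that are too narrow would affect the primary comparison and every secondary comparison made with the same tests.

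This is not a detail left to an analysis plan: the article names the tests.

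**Working it through.** **Inputs from the protocol article.** 160 patients, 80 per arm, 20% difference, 80% power (Sample size); 16 and 18 therapists (Physiotherapists and Interventions).

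**Assumptions, because the article does not give them.** Two-sided alpha 5%; ICC from 0.01 to 0.10; caseload CV of 0 or 0.6; the 20% difference read as percentage points; base rates as shown.

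**1. The plan's own figure.** "160 patients are needed to detect this difference" cannot be fully checked without alpha and base rates. For independent patients, 20% vs 40% at two-sided 5% and 80% power gives

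n = [1.96·√(2·0.3·0.7) + 0.8416·√(0.2·0.8 + 0.4·0.6)]² / 0.2² = (1.270 + 0.532)² / 0.04 ≈ 81.2, so 82 per arm, 164 in total.

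That is within 3% of 160. Mid-range rates (30% vs 50% to 40% vs 60%) need 186 to 194. The figure is thus reachable under some inputs with no clustering allowance.

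**2. Mean caseload.** PT: 80/16 = 5.0. GAP: 80/18 = 4.44.

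**3. Design effect per arm.** DE = 1 + [(1 + CV²)·m − 1]·ICC, averaged over the arms. At ICC 0.05:

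- CV 0: PT 1 + 4·0.05 = 1.200; GAP 1 + 3.44·0.05 = 1.172; mean 1.186.
- CV 0.6: PT 1 + 5.8·0.05 = 1.290; GAP 1 + 5.04·0.05 = 1.252; mean 1.271.

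**4. Actual type I error of a nominal 5% test that ignores clustering.** 2·[1 − Φ(1.96/√DE)]. At DE 1.186: 1.96/1.089 = 1.80, which gives 7.2%.

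| Assumed ICC | DE, CV 0 | Type I, CV 0 | DE, CV 0.6 | Type I, CV 0.6 |
|---|---|---|---|---|
| 0.01 | 1.037 | 5.4% | 1.054 | 5.6% |
| 0.02 | 1.074 | 5.9% | 1.108 | 6.3% |
| 0.05 | 1.186 | 7.2% | 1.271 | 8.2% |
| 0.10 | 1.372 | 9.4% | 1.542 | 11.5% |

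**5. Simulation check.** Beta-binomial outcomes, 16 and 18 therapists with near-equal caseloads, uncorrected Pearson chi-square, 40,000 runs per setting, improvement rate 0.5. Rejection of a true null was 4.7% at ICC 0, then 5.2%, 5.6%, 6.9% and 9.0% at ICC 0.01, 0.02, 0.05 and 0.10. This agrees with the formula to within about half a point.

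**6. Power.** Effective n per arm is 80/DE. For 20% vs 40%, 80 independent patients per arm give 79%. At ICC 0.05 the effective n is 80/1.186 = 67.5 and power is 72%; with CV 0.6 it is 80/1.271 = 62.9 and power is 69%. To hold the power that 160 independent patients give, the total would be 160·1.186 ≈ 190, or 160·1.271 ≈ 204.

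**The case against.** The strongest reply is that the size of the problem is assumed. The protocol gives no ICC, and caseloads average fewer than five, so at ICC 0.01 to 0.02 the inflation with equal caseloads is under one percentage point. The PT standardisation meeting, the consensus on goals and techniques, and the two-day GAP course could all reduce variation between therapists. This stands: the size is conditional, and at the low end it is small.

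Two features may also offset part of the inflation. The article does not say which version of the chi-square test is meant. With a continuity correction and near-equal caseloads, simulated type I error was 4.1% at ICC 0.02 and 4.9% at 0.05, and it passed 5% at 0.10 (7.0%), or at 0.05 with uneven caseloads (6.3%). Randomisation is also stratified on gender, age and severity, and an unadjusted test after such stratification tends to be conservative, by an amount that cannot be worked out here. Both points stand, but neither corrects for clustering: any offset is accidental.

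A reader might infer that type I error necessarily exceeds 5%, or that caseloads are in fact unequal. The article supports neither. Patient choice permits unequal caseloads, but no distribution is given, and the CV of 0.6 is illustrative. Patient choice could also make one therapist's patients alike through case mix rather than through treatment; an observed ICC would then overstate the therapist effect.

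**Conclusion.** The point holds in conditional form. Therapists are wholly nested within arm and the named tests ignore this, so the standard error of the treatment contrast is understated for any positive therapist ICC. With equal caseloads the multiplier it needs is 1.02 at ICC 0.01, 1.09 at 0.05 and 1.17 at 0.10; with CV 0.6 it is 1.03, 1.13 and 1.24. The type I errors in the table rest on an assumed two-sided 5% level, an assumed ICC and the uncorrected test. They range from negligible to roughly double the nominal level. The direction does not depend on those assumptions; whether the final error rate is above 5% does.

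**What to change.** Before the data are seen, replace the independent-patient tests with one named analysis per type of outcome.

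- **Primary dichotomised GPE:** for example a risk difference with cluster-robust variance by therapist and a small-sample correction for 16 and 18 clusters. This stays on the scale on which the trial was sized; a mixed logistic model would give a conditional odds ratio instead.
- **Continuous outcomes:** a linear mixed model with a therapist random intercept and Satterthwaite or Kenward-Roger degrees of freedom.
- **Reporting:** the estimated ICC and the caseload distribution per arm.
- **Data:** confirm that the treating therapist is recorded for each patient. The article mentions a session form but does not list its fields, so this should not be taken for granted.
- **Sample size text:** restate "In this calculation a power (1 - β) of 80% is taken into account" as conditional on an assumed ICC, with alpha and base rates given.

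If the treating therapist is recorded, the change needs no extra visits or measurements. Its real cost is wider intervals and power below 80% unless the ICC is near zero. Holding the planned power at ICC 0.05 would take about 190 patients with equal caseloads, or 204 with CV 0.6, instead of 160. If recruitment cannot be extended, the lower power should be stated openly.

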## Discussion

This study is designed to evaluate the clinical and cost effectiveness of a behavioural graded activity programme compared with a physiotherapy treatment in patients with chronic non-specific neck pain. Since physiotherapists perform both treatments in this study, contrast between the two treatments is a very important issue. There are contrasts both in the composition of the treatment and the way the physiotherapists approach the patient. With regard to the composition, the graded activity programme (GAP) starts with a systematically performed baseline measurement; this is in contrast to the physiotherapy treatment (PT), where treatment is based on history taking and physical examination. In GAP quotas are set based on the patient's behaviour, whereas in PT they are set based on pain levels and training principles. After quotas are set GAP uses a time-contingent treatment approach, which involves a pre-set systematic increase in activities. In contrast, PT uses a pain-contingent approach, which means that treatment is adapted to the patient's reaction to previous treatment sessions. Furthermore, GAP uses a hands-off approach, whereas PT may contain hands-on techniques, such as massage, traction etc (Table 1).

This study addresses an important question because chronic neck pain is a common complaint and it remains unclear which type of physiotherapeutic treatment is most effective. Recruitment of patients will take place until up to the end of 2004; follow-up measurement will continue up to end 2005.
